## Methods

### Implementation Study

This is an implementation multicentric study. The PARACT study is part of the realistic evaluation of an intervention as described by Pawson and Tilley following Campbell’s work [64]. This approach favors multisite and multidisciplinary assessments to study the interactions of context-mechanism-outcomes configurations. This type of evaluation makes it possible to adapt the interventions according to the results observed, while considering the context. The assessment selected for this study will therefore be multidisciplinary, combining public health teams and human and social sciences teams. The aspect of navigation in establishments will be assessed in accordance with current recommendations [65]. The patient will act as his/her own control. Given that we are conducting a study of an implementation that is complex, the study will follow the RE-AIM (Reach, Effectiveness, Adoption, Implementation, and Maintenance) framework. The implementation process will consist of 3 stages (Figure 1).

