### Statistical Analysis

#### Design

The analyses will be performed using R 3.2.5 (R Foundation [83]) software. The characteristics of the patients will be described using the following statistics: for quantitative variables, number of available data, means, standard deviation, median, quartile 1, and quartile 3; and for qualitative variables, absolute and relative frequencies (expressed as percentage). To calculate patient activation, the guidelines provided by Insignia Health will be followed [84]. Activation will be measured quantitatively at enrollment, at 6 months, and at 12 months. The difference will be calculated between the baseline measurement and the 12-month measurement for all patients at each center. The mean of this difference will be compared between the comprehensive cancer center that employs a nurse navigator and each of the 4 other facilities. Activation will also be compared according to its evolution during the 12 months of follow-up by using a mixed linear model. The variables influencing the difference in the activation score will be included in this model. The search for factors influencing the activation level will be carried out using the following methods:

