Initially, univariate analysis with chi-squared tests (or Fisher exact if the conditions are not met) for qualitative variables and Student two-sided *t* test (or Wilcoxon test if the conditions are not met) for quantitative variables will be performed.Subsequently, multivariate analysis with all exploratory variables with a significance threshold lower than 0.2 will be introduced into the multivariate model. The interactions between the variables will be ensured in advance. If an interaction is detected, the choice of the variable to be introduced will be made based on clinical relevance. The choice of the best multivariate model will be made using a selective downward procedure on the Akaike information criteria.Health literacy will be assessed via the score obtained by the REALM-R (a score <6 demonstrating a low health literacy score). The before/after health literacy increase will be assessed using a McNemar chi-square test using the score qualitatively (threshold at 6). A logistic regression model with random effect will be used in the multivariate analysis to eliminate any confounding factors with the same methodology as described above. The same methodology will be applied to the HAD scale (threshold at 11). The analysis of quantitative scales such as the EQ-5D-3L or the confidence level will be performed with matched (or otherwise Wilcoxon) Student tests between inclusion and M12. Random multivariate linear models will be implemented to adjust for any confounding variables. For the EQ-5D-3L, analyses of time until deterioration can be implemented if necessary.

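### On detecting an interaction the plan keeps one variable by clinical relevance, a remedy for collinearity that hides effect modification in the adjusted models

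*Protocol article*

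**What the plan says.** The rule stands in the protocol article under Statistical Analysis, Design. The procedure is introduced with "The search for factors influencing the activation level will be carried out using the following methods" and then runs in this order:

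- Univariate tests are done first, and the entry rule follows: "multivariate analysis with all exploratory variables with a significance threshold lower than 0.2 will be introduced into the multivariate model".
- Interactions are examined: "The interactions between the variables will be ensured in advance".
- The rule at issue: "If an interaction is detected, the choice of the variable to be introduced will be made based on clinical relevance".
- Final selection: "The choice of the best multivariate model will be made using a selective downward procedure on the Akaike information criteria".

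Two statements extend its reach. For the mixed linear model of activation over 12 months, the same section says "The variables influencing the difference in the activation score will be included in this model". For health literacy (REALM-R) it says "A logistic regression model with random effect will be used in the multivariate analysis to eliminate any confounding factors with the same methodology as described", which points back to the steps just listed, and the HAD scale then takes the same methodology.

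The article nowhere mentions a product term, keeping both main effects, or reporting effects by level of a modifier. It does not mention correlation or collinearity between predictors either.

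**The concern.** If two predictors carry overlapping information, keeping the clinically more useful one is ordinary practice. An interaction is a different matter: the effect of A is not the same at each level of B. Describing that needs A, B and A×B. A rule that answers a detected interaction by choosing one variable discards what is needed to report the finding that triggered it.

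Two things are at stake. First, the retained coefficient can hide effects that differ between strata or even have opposite signs. Second, the dropped variable no longer adjusts for anything. In the REALM-R and HAD models, whose stated aim is to remove confounding, that can work against the purpose of the model.

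The rule also sits awkwardly with the study's approach. The Implementation Study section adopts a realist evaluation "to study the interactions of context-mechanism-outcomes configurations", so effects that vary with context are of direct interest.

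**Working it through.** **Is there a figure to reproduce?** No. The plan gives no effect size, SD or power for these models. The check is therefore the logic of the rule, with an illustration on assumed inputs.

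**Assumed inputs.** Two binary factors A and B, each with prevalence 0.5; correlation φ of 0 or 0.3; residual SD 1; a linear outcome

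y = a·A + b·B + g·A·B + e.

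The true effect of A is a when B = 0 and a + g when B = 1. Its average over the sample mix is a + 0.5g.

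**Coefficient when only A is kept.** Let p1 = P(B=1 | A=1) and p0 = P(B=1 | A=0). Then

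coefficient = a + b(p1 − p0) + g·p1.

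With prevalence 0.5, p1 = 0.5 + 0.5φ and p0 = 0.5 − 0.5φ. At φ = 0 both are 0.50. At φ = 0.3 they are 0.65 and 0.35.

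| a, b, g | True effect, B=0 / B=1 | Average | A only, φ=0 | A only, φ=0.3 |
|---|---|---|---|---|
| 0, 0.3, 0.5 | 0.00 / 0.50 | 0.25 | 0.25 | 0.09 + 0.325 = 0.415 |
| 0.3, 0.3, −0.6 | 0.30 / −0.30 | 0.00 | 0.00 | 0.30 + 0.09 − 0.39 = 0.00 |
| 0.2, 0, 0.4 | 0.20 / 0.60 | 0.40 | 0.40 | 0.20 + 0 + 0.26 = 0.46 |
| 0.2, 0.4, 0 | 0.20 / 0.20 | 0.20 | 0.20 | 0.20 + 0.12 = 0.32 |

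**Simulation check.** 2,000 data sets of 600 patients (the enrollment cap, 3 × 150 + 2 × 75 = 600) gave, for A only at φ = 0 and φ = 0.3: 0.252 and 0.418; 0.000 and 0.000; 0.396 and 0.461; 0.198 and 0.320. These agree with the formula to within 0.005. Fitting A, B and A×B recovered the true stratum effects to within 0.01 in every row at both correlations.

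**What the rows show.**

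- Row 1, φ = 0: 0.25 is a correct average, but it describes neither stratum.
- Row 1, φ = 0.3: A and B without the product still give 0.25, so the excess of about 0.17 comes from dropping B.
- Row 2: opposite effects vanish into zero.
- Row 3: B has no effect of its own when A = 0, yet dropping it still shifts the estimate from 0.40 to 0.46 at φ = 0.3, because it acts through the product.
- Row 4 has no interaction. It isolates the cost of omitting a correlated covariate: 0.32 against 0.20.

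The arithmetic is for a linear model. The mechanism carries over to the logistic models for REALM-R and HAD, but these figures do not.

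**The case against.** **Collinearity may have been meant.** The choice of a variable before the multivariable model is fitted looks like handling of overlapping predictors, and the English of the section is loose. This may well be the intention, and it cannot be excluded. It does not rescue the sentence, which speaks only of interaction. Under that reading the text names the wrong concept, gives no criterion, and leaves real interactions without a rule.

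**The retained coefficient is not always wrong.** A reader might infer that the rule always yields a biased effect. It does not. With uncorrelated factors in a linear model, the coefficient is a valid average over the sample mix. Bias from omission needs a correlation between the two variables and an effect of the dropped one on the outcome.

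**The screen may do the damage first.** In a perfectly balanced crossover, the factor has no marginal effect. With assumed effects of +4 and −4 points, SD 15 and n = 400, it passed the univariate threshold in only 21% of simulated runs. If the screen comes before the interaction check, most of the loss in that extreme case belongs to the screen. The article does not settle the order. The milder rows above do not depend on such a symmetric crossover.

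**Context is studied elsewhere too.** A reader might infer that the rule erases the study's evidence on context. The site interviews, the RE-AIM outcomes and the direct comparison of centers do not pass through it, so that inference fails.

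**The choice is not purely data-driven.** The trigger is a detected interaction, but the stated criterion is clinical relevance. That stands.

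**Conclusion.** The sentence is wrong as written and should be changed. Choosing one variable does not answer a detected interaction. It leaves an average that hides differing stratum effects, and a confounded one if the dropped variable is correlated with the retained one and affects the outcome.

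The reach is limited to the search for factors influencing activation, the mixed model that takes up the selected variables, and the adjusted REALM-R and HAD models. The unadjusted comparison of mean 12-month change between centers, the McNemar tests and the paired tests are unaffected. The sentence on adjusted models for the EQ-5D-3L does not say that it uses the same selection method, so the point is not extended to them.

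The size cannot be stated for this study. The figures of 0.25 and about 0.42 against true stratum effects of 0.00 and 0.50 SD rest entirely on assumed effects, prevalences and correlation. They show the mechanism, not an expected error.

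**What to change.** Replace the sentence with: *If an interaction is detected, both variables and their interaction term are kept and effects are reported by level; if two variables are strongly collinear, the clinically more relevant one is kept.* If only collinearity was intended, say so and give the criterion; a rule for true interactions is still needed.

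Limit interaction testing to a few interactions that the study team specifies in advance. Which ones is for the team to decide.

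The cost is a small edit to the analysis section, with no change to data collection. The models gain a few parameters: one per pair of binary factors, and 5 − 1 = 4 for a binary factor crossed with five centers. Stratum-level estimates are less precise. In the balanced, uncorrelated illustration each stratum holds half the patients, so the standard error rises by √2, from 2/√600 = 0.082 to 2/√300 = 0.115 SD.

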##### Validity and Reliability of the Questionnaires

The PAM-13 was developed by Hibbard et al to assess knowledge, skills, and confidence in managing health [30,31,77]. It is used in several contexts of disease and in many countries around the world [31,33-39]. Specifically, Prey et al have demonstrated its reliability and validity with inpatient individuals in oncology [40]. The validated French version will be used. The HAD scale will be used to measure the evolution of patients’ anxiety [78]. The United Kingdom National Health Service and French National Authority for Health recommend its use to assess anxiety and depression among inpatient individuals. Its reliability and validity are widely recognized [78-80]. The EQ-5D-3L is a validated tool for measuring the quality of life [81]. Several studies have been published and have provided evidence to support the validity and reliability of the EQ-5D in studies of cancer [82]. This self-questionnaire explores 5 dimensions: mobility, self-care, usual activities, pain/discomfort, and worry/pressure. The REALM-R test validated in French will be used to measure the level of patients’ health literacy. Bass et al provided evidence to support the validity and reliability of the shortened version of the REALM, which is named as REALM-R [26]. Grandjacquot recently adapted it in the French language, and it proved effective in detecting inadequate levels of health literacy [27].

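### HAD and REALM-R are tested for change only after being cut at a threshold, which gives up power that the full scores would keep

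*Protocol article*

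**What the plan says.** All of this is in the protocol article.

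- **REALM-R.** Low literacy is defined by the cut, "a score <6 demonstrating a low health literacy score". For change, "The before/after health literacy increase will be assessed using a McNemar chi-square test using the score qualitatively (threshold at 6") (Statistical Analysis, Design).
- **HAD.** "The same methodology will be applied to the HAD scale (threshold at 11") (same section).
- **Adjusted analysis of both.** "A logistic regression model with random effect will be used in the multivariate analysis to eliminate any confounding factors" (same section). The outcome of that model is again the dichotomy.
- **Other scales.** "The analysis of quantitative scales such as the EQ-5D-3L or the confidence level will be performed with matched (or otherwise Wilcoxon) Student tests", comparing inclusion with month 12 and followed by linear models. Activation is analysed as a number, with a linear mixed model over the 12 months.
- **Purpose of the two instruments.** "The HAD scale will be used to measure the evolution of patients’ anxiety" and "The REALM-R test validated in French will be used to measure the level of patients’ health literacy" (Validity and Reliability of the Questionnaires).

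No analysis of the uncut HAD or REALM-R score is stated. Both are secondary measures, collected at enrolment, 6 months and 12 months.

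**The concern.** McNemar's test uses only the pairs that cross the cut. With HAD cut at 11, a patient who goes from 18 to 12 and a patient who goes from 10 to 4 are both concordant and add nothing to the test. The random-effect logistic model does not recover this information, because it is fitted to the same binary variable.

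That fits poorly with an instrument meant to follow the evolution of anxiety, and with the treatment of activation, EQ-5D-3L and the confidence level, all kept on their full range. The article gives no reason for the difference. At stake is the chance of detecting modest change in two of the three named secondary measures (HAD, EQ-5D-3L, REALM-R). Enrolment is capped by budget and missing values are not imputed, so extra patients are not available to make up the loss.

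**Working it through.** **The plan's own figure.** The article states no power for these outcomes, so none can be reproduced. Its enrolment cap does reproduce: 3 × 150 + 2 × 75 = 600. McNemar needs both measurements, so 600 pairs is the upper limit and attrition lowers it. The article gives no attrition figure; 300 and 420 pairs below are assumptions.

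**Assumed inputs, because the article gives none.** HAD anxiety score as an integer from 0 to 21, SD 4, baseline mean 7.5, correlation 0.6 between the two times, two-sided 5% test, McNemar without continuity correction.

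**Formulas.** Let p10 be the proportion leaving the above-cut group and p01 the proportion entering it, with pd = p10 + p01 and d = p10 − p01. Let δ be the mean shift in SD units and ρ the correlation.

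- McNemar: n = (1.96·√pd + 0.8416·√(pd − d²))² / d² for 80% power.
- Paired test on the score: n = 2(1 − ρ)·((1.96 + 0.8416)/δ)².

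**Worked example.** Take ρ = 0.6, 20% of patients above the cut at baseline, and δ = 0.15. Cutting a bivariate normal at that point gives p10 = 0.1148 and p01 = 0.0755, so pd = 0.1903 and d = 0.0393.

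- McNemar: (1.96 × 0.4362 + 0.8416 × 0.4345)² / 0.001545 ≈ 964 pairs.
- Paired test: 0.8 × (2.8016/0.15)² ≈ 279 pairs.
- Power, McNemar against paired test: 34% against 83% with 300 pairs, and 60% against 98% with 600.

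With ρ from 0.5 to 0.8, the smaller side of the cut from 10% to 50%, and δ from 0.10 to 0.20, McNemar needs 2.1 to 8.5 times as many pairs.

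**Simulation on the bounded HAD-type score** (rounded and truncated bivariate normal, inputs as above):

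| Pairs | Mean fall (points) | McNemar, cut 11 | Paired t, full score |
|---|---|---|---|
| 420 | 0.5 | 36% | 80% |
| 600 | 0.5 | 48% | 92% |
| 300 | 0.75 | about 52% | 95% |
| 600 | 0.75 | 82% | about 100% |
| 600 | 1.0 | 96% | 100% |

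In these runs about 88% of patients change score, but only about 20% cross the cut.

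**Sensitivity (300 pairs, 0.75-point fall).** McNemar against paired t is 44% against 84% at correlation 0.4, and 68% against 100% at 0.8. With the baseline mean at the cut itself (11), which favours McNemar most, it is 66% against 95%.

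**REALM-R.** With an assumed range of 0-8, SD 2, correlation 0.7, a rise of 0.3 and baseline means of 5.5 to 7.5, McNemar has 34-54% power against 74-87% with 300 pairs, and 59-83% against 96-99% with 600. The direction is the same, but every input is assumed.

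**The case against.** The strongest defence is that nothing here is wrong. McNemar is a valid test for paired binary data and both cuts are fixed in advance. The outcomes are secondary, and the article says outright that no sample size can be derived for an efficacy hypothesis. All of this stands, and it makes the point one of efficiency.

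For REALM-R the defence goes further. The article calls it a screening instrument and supports the French version as effective in detecting inadequate literacy. A shift between low and adequate literacy is then a result in its own right. This also stands: it justifies keeping the binary analysis, though not having it as the only test of an increase.

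The power figures are assumption-bound. The statistical section applies the cut of 11 to the HAD scale without naming a subscale; if another score is meant, the figures do not carry over. For larger shifts near 600 pairs, both tests do well.

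Two stronger readings may tempt a reader.

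- *Dichotomising throws away the month-6 data.* McNemar does omit month 6, but so does the paired EQ-5D-3L test, which compares inclusion with month 12. The text does not restrict the random-effect logistic model to two time points, so it could use month 6. This does not separate the two approaches.
- *Real changes will be declared absent.* No rule in the article treats a non-significant result as proof of no change. A lower chance of detection is all that follows.

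**Conclusion.** The point holds as an avoidable loss of efficiency in two secondary outcomes. It is clearest for HAD, where the stated purpose is to follow anxiety over time. For REALM-R it is weaker, because the threshold has a screening use of its own.

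The direction is secure: the full-score test had more power in every scenario tried, apart from shifts large enough for both to approach 100%. The amount is not secure, because range, SD, correlation, baseline mean and shift are all assumed. On those assumptions the loss matters for falls of about half to three-quarters of a point or for reduced numbers of pairs, and is minor for a 1-point fall with all 600. The documents do not support calling the planned test invalid or the threshold results meaningless.

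**What to change.** In Statistical Analysis, Design:

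1. Make the full-score analysis the main test of change for HAD, and name the score used. Either the paired t or Wilcoxon test already planned for EQ-5D-3L, or the linear mixed model already planned for activation, fitted to months 0, 6 and 12, would serve.
2. Add the same full-score analysis for REALM-R.
3. Keep the McNemar and random-effect logistic results at 6 and 11 as supportive analyses.

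The change is to analysis wording only and needs no new data. The cost is one more analysis per scale and a headline mean change that is less directly clinical than a shift between categories; the retained threshold results supply that reading.

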#### Methods for Considering Missing, Unused, or Invalid Data

No imputation of missing values will be performed.

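### The random-effect models cannot eliminate confounding of the before/after changes in REALM-R, HAD and EQ-5D-3L in a study without controls, and the plan should not say that they do

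*Protocol article*

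**What the plan says.** The design is uncontrolled. Under Implementation Study the protocol article states: "The patient will act as his/her own control". Questionnaires are completed at enrollment, 6 months and 12 months.

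Under Statistical Analysis, Design, the secondary outcomes are analysed as changes from before to after. For REALM-R: "The before/after health literacy increase will be assessed using a McNemar chi-square test using the score qualitatively (threshold at 6". HAD is treated the same way with a cut-off of 11. The analysis of EQ-5D-3L "will be performed with matched (or otherwise Wilcoxon) Student tests between inclusion and M12".

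Each test is followed by a model with a stated purpose. For the binary outcomes: "A logistic regression model with random effect will be used in the multivariate analysis to eliminate any confounding factors". For the quantitative scales: "Random multivariate linear models will be implemented to adjust for any confounding variables". Covariates for the binary model are to be found by the method set out just before for the activation level: "multivariate analysis with all exploratory variables with a significance threshold lower than 0.2 will be introduced into the multivariate model", followed by backward selection on the Akaike criterion. On missing data the article says: "No imputation of missing values will be performed".

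**The concern.** Read in order, the models are the adjusted versions of the before/after tests, and the article credits them with removing any confounding of those changes. A factor with the same value at both visits cannot confound a within-patient change, so adjusting for it removes nothing. What can confound the change runs alongside the calendar of the study. Patients enter within 15 days of the consultation announcing the cancer (Screening and Inclusion), and all are being treated with intravenous chemotherapy or immunotherapy (Patient Inclusion Criteria). Adjustment to the diagnosis, treatment phase and disease course therefore all unfold between M0 and M12.

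At stake is how the results are reported. A change in literacy, anxiety or quality of life could be published as adjusted for any confounding while the time-related influences are untouched. A second estimate that nearly duplicates the first could also be taken as independent support.

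**Working it through.** **Inputs.** From the article: two-visit comparison M0 to M12, no control group, no imputation, and a cap of 600 patients. The cap reproduces: 3 × 150 + 2 × 75 = 600. It is a budget limit, and the article gives no effect size, SD, dropout rate or adjusted result to reproduce. All effect sizes, covariates and missingness rates below are therefore assumptions, used with N = 600 and two visits.

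**Step 1: algebra for complete pairs.** Let y(i,0) = a(i) + g·x(i) + e(i,0) and y(i,12) = a(i) + g·x(i) + d + e(i,12), where x is fixed for the patient. Then y(i,12) − y(i,0) = d + e(i,12) − e(i,0). Both a and g·x drop out. If a time-varying factor u also acts with slope h, the mean difference estimates d + h × mean[u(12) − u(0)]. No fixed covariate touches the second term. If u rises by nearly the same amount in everyone, as time since diagnosis does here, it is nearly collinear with visit and no model on these data can separate the two.

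**Step 2: complete pairs, fixed covariates as main effects.**
- Linear: 0.02136 (SE 0.00570) from the paired difference, and the same estimate and SE from the random-intercept model with and without age and sex.
- Logistic: log odds ratio 0.491 from McNemar, ln(b/c) with b and c the two discordant counts; 0.491 from the random-intercept model; 0.490 with age and sex. This is nearly, not exactly, unchanged.

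**Step 3: complete pairs, with a time-varying confounder present.**

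| Analysis | Linear (truth 0.03) | Log odds ratio (truth 0.5) |
|---|---|---|
| Paired difference / McNemar | 0.0722 | 1.055 |
| Random-effect model, visit only | 0.0722 | 1.055 |
| plus age and sex | 0.0722 | 1.052 |
| plus the time-varying factor itself | 0.0195 (SE 0.007) | 0.688 (SE 0.17) |

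Fixed covariates leave the bias in place. Only the confounder itself, if measured, moves the estimate.

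**Step 4: incomplete follow-up.** M12 dropout of about 31% was made to depend on age and baseline score. The paired test kept 416 patients and the mixed model used 600. Mean estimates over 60 runs (truth 0.030) were 0.009 paired, 0.022 mixed model, and 0.030 mixed model with age and sex. Here covariates matter, because they predict who is lost.

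**Step 5: missing covariates.** With an assumed 20% missing rate on a covariate and those rows dropped, 492 of 600 patients remained in the run. The adjusted estimate was 0.02455 (SE 0.00633), equal to the paired estimate in the same 492. With k covariates each missing independently at rate p, the loss is 1 − (1 − p)^k:
- 5 at 3%: 1 − 0.97^5 = 14%
- 8 at 3%: 1 − 0.97^8 = 22%
- 8 at 5%: 1 − 0.95^8 = 34%

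**The case against.** The strongest reply is that the article does not limit the models to fixed covariates. It collects contacts with nurses and other professionals over 12 months, and it measures several scales at three visits. Any of these could enter as time-varying covariates, and step 3 shows that such a covariate can move the estimate a long way. This stands, and it rules out saying that the models adjust for nothing. It does not rescue the claim of elimination. Contacts are part of the care under study and may be mediators. The screening tests named (chi-squared, Fisher, Student, Wilcoxon) are suited to one value per patient. Without controls, whatever is unmeasured or collinear with visit remains.

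A reader might also infer that the adjusted result is simply the crude number from fewer patients, so that any gap between the two reflects lost patients. The documents do not support this. Step 4 shows the reverse can happen: a random-effect model keeps patients without an M12 value, and baseline predictors of dropout can move the estimate toward the truth. Patients are lost only if covariates are missing and their rows are dropped, and the article gives no rate for that.

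The models may also be meant to find factors associated with the level of each outcome, since they borrow the method of the search for factors influencing activation. Mutual adjustment would then change those coefficients legitimately. The text, however, attaches the models to before/after tests. The covariate list and target coefficient may properly sit in a fuller document, and their absence is not the point here. Finally, these outcomes are secondary, the article disclaims an efficacy hypothesis, and it is open about the patient being his or her own control. That lowers the severity.

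**Conclusion.** The concern holds as a claim that the analysis cannot meet. For fixed covariates entered as main effects in complete pairs, the time effect is unchanged exactly in the linear model and almost exactly in the logistic one (a shift of 0.001 to 0.003 on the log-odds scale in steps 2 and 3). Time-related influences stay mixed with the M0 to M12 effect. Correcting for selective dropout is a real benefit of the planned model class, but it addresses who is observed at M12 and not what else changed over the year. The algebra needs no assumption beyond complete pairs and fixed covariates. The sizes in steps 3 to 5 depend on simulated effects, dropout and missingness, and they show direction rather than forecast this study. Severity is minor to moderate.

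**What to change.** In Statistical Analysis, Design:

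1. Delete the two statements that the models eliminate or adjust for any confounding.
2. Make a patient-level mixed model (linear or logistic) with visit (M0, M6, M12) as a factor the estimate of change, using all patients with any visit, in place of relying on M0 to M12 paired tests.
3. Do not choose covariates for the time effect by p < 0.2 and the Akaike criterion. Include baseline predictors of dropout named in advance.
4. For the question of which patients change, fit covariate-by-visit terms.
5. State that the time effect is not separated from adaptation after diagnosis and treatment phase.

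The cost is a little more modelling work and the loss of the adjusted-for-confounding label. The mixed model also assumes that dropout depends only on observed data, which should be said when the results are reported.
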